### Diet, physical activity and sedentary behaviour

#### 24-h food recall

Diet will be assessed by a 24-h food recall completed using the Automated Self-Administered 24-Hour Dietary Assessment Tool (ASA24) [70]. Participants will be prompted to record type and quantity of foods, drinks and supplements consumed over a 24-h period using an Australian-specific food database.

#### Objectively measured physical activity

Habitual physical activity and sedentary behaviour will be objectively assessed over seven consecutive days using hip-mounted ActiGraph GT3X (ActiGraph, Pensacola, FL, USA) and thigh-mounted activPal accelerometers (PAL technologies, Glasgow, Scotland) [71].

#### Self-reported physical activity

Self-reported weekly physical activity over the preceding month will be assessed using the CHAMPS questionnaire [72]. For the baseline assessment participants will be asked to recall their typical physical activity prior to diagnosis.

### Health and treatment-related information

A general lifestyle questionnaire will be used to collect information relating to participant age, health status and medical history, cardiovascular medications and cardiovascular risk profile. Clinical variables related to cancer diagnosis and treatment histopathology, previous and current therapy, chemotherapy regime and treatment response will be obtained from participant medical records. The average relative dose intensity of the originally planned chemotherapy regimen that is received will be calculated according to standard formulae [73], and will be used as a measure of treatment completion. The presence and concentration of tumour infiltrating lymphocytes, in addition to the Miller-Payne grading for patients receiving neoadjuvant chemotherapy will be used to explore the potential for exercise to modulate the tumour response to neoadjuvant therapy.

### ET adherence and attendance

Attendance and adherence to the prescribed number of exercise sessions, and dose within each exercise session (both supervised and unsupervised) throughout the 12-month intervention will be assessed using the Physitrack online patient software which will be logged by participants during each session. Attendance will be calculated from the number of sessions completed versus number prescribed per week. Adherence to the aerobic training will be calculated from the prescribed vs completed duration and intensity of aerobic exercise, whilst adherence to the resistance training will be assessed from the prescribed vs completed repetitions and weight. For the supervised sessions during Phase 1 and 2, trainers will record reasons for modification (increase or decrease) to the prescribed dose of aerobic and/or resistance exercise during each session.

### Adverse events

The occurrence of any adverse events (AEs) will be collected at each testing visit via face to face interview. Participants in the exercise training group will also be asked about the occurrence of an AE at each training session. An event will be considered an AE where there is any possibility that the event related to a study procedure or the exercise intervention. An AE will be classified as a serious AE if it results in death, is immediately life threatening, requires inpatient hospitalisation, requires prolongation of existing hospitalisation, or results in persistent or significant disability/incapacity.

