**Methods:**

One hundred women with early-stage BCa (40–75 years) scheduled for AC will be randomized to 12-months of structured exercise training (*n* = 50) or a usual care control group (*n* = 50). Participants will be assessed at baseline, 4-weeks following completion of AC (4-months) and at 12-months for all measures.

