### Randomisation and blinding

Following baseline testing, each participant will be randomly allocated (1:1 ratio) to the intervention or control group by an independent researcher using a computer-generated, random number sequence with the outcome communicated via telephone. Stratified block randomisation will be used, with participants stratified by age (< 60 or ≥ 60 years) and human epidermal growth factor receptor 2 (HER2) status (positive or negative), with block sizes alternating between two and four participants. Participants, care providers and outcome assessors will not be blinded to group allocation. However, the quantification of all cardiac imaging (echocardiography and cardiac magnetic resonance imaging, CMR) will be performed by researchers blinded to subject identity. Furthermore, outcome assessors will be blinded to pre-chemotherapy values for all assessments.

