#### Phase 1 – structured exercise during AC (week 1–12)

The exercise training program conducted during AC will consist of 30–60 min of supervised, multi-modal exercise training performed three times per week. Sessions will use a combination of aerobic and progressive resistance training (PRT) and will be conducted at the Baker Heart and Diabetes Institute, the Deakin University Clinical Exercise Learning Centre, and participating health and fitness centres throughout metropolitan Melbourne. Sessions will be prescribed and overseen by an Accredited Exercise Physiologist (AEP), with all training supervised by appropriately trained AEPs and/or Exercise Scientists. A novel, non-linear step periodization model will be used due to its ability to adjust for fluctuations in each participant’s symptoms throughout their chemotherapy cycles whilst still allowing for adequate progression of training volume [46]. The model used in this study will involve a progressive increase in exercise volume of ~ 5–10% each week until the week immediately following each participant’s chemotherapy cycle. This week will be considered a ‘de-loading’ week where training intensity will be reduced by ~ 5%.

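### Adverse events are defined by relatedness and elicited at training sessions in the exercise arm only, so the AE and SAE counts cannot support a fair between-arm safety statement

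*Protocol article*

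**What the plan says.** The Adverse events section of the protocol article sets three rules.

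- **Definition.** "An event will be considered an AE where there is any possibility that the event related to a study procedure or the exercise intervention". No category is described for events of any cause.
- **Seriousness.** "An AE will be classified as a serious AE if it results in death, is immediately life threatening, requires inpatient hospitalisation", or if it meets one of the remaining seriousness criteria. What is classified is an AE, so an event must first pass the relatedness condition.
- **Collection.** For everyone, "The occurrence of any adverse events (AEs) will be collected at each testing visit via face to face interview". For one arm there is more: "Participants in the exercise training group will also be asked about the occurrence of an AE at each training session".

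The schedule comes from elsewhere in the article. The abstract's Methods paragraph says: "Participants will be assessed at baseline, 4-weeks following completion of AC (4-months) and at 12-months for all measures". Under Randomisation and blinding: "Following baseline testing, each participant will be randomly allocated (1:1 ratio) to the intervention or control group". Under Usual care group, controls get no supervised exercise from the research team. Under Data management, there is no formal data monitoring committee.

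**The concern.** Relatedness is normally an attribute recorded about an adverse event. Here it is the condition for being one. The two arms are not equally exposed to the things an event could be related to. The exercise arm has the exercise programme and the testing procedures, while usual care has the testing procedures only. The same hospital admission during chemotherapy could therefore be a serious adverse event in an exerciser and not an adverse event at all in a control.

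The second asymmetry is in how often participants are asked. Events found by frequent questioning in one arm, and by recall over months in the other, give different counts even when the true rates are equal.

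At stake is what the trial can say about safety. It studies exercise, including high-intensity intervals, during cardiotoxic chemotherapy, and the Discussion hopes to inform exercise and cardio-oncology guidelines. Readers will expect adverse events by arm. If the stated rule is followed, an excess in the exercise arm could come from the definition and the questioning alone. A real effect of exercise on clinical events judged unrelated would not appear in the AE counts.

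**Working it through.** There is no stated safety figure to reproduce. The check compares the two arms under the stated rules and counts the planned occasions for questioning.

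**1. Routes by which an event can qualify**

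| Possible relation | Exercise arm | Usual care |
|---|---|---|
| Study (testing) procedure | yes | yes |
| Exercise intervention | yes | no |
| Neither | not an AE | not an AE |

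The seriousness rule applies to AEs, so the table holds for serious events too.

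**2. Planned occasions for questioning after randomisation**

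Randomisation follows baseline testing, so the shared time points are 4 and 12 months: 2 in each arm.

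Training sessions, exercise arm only:
- Phase 1, 12 weeks of "30–60 min of supervised, multi-modal exercise training performed three times per week": 12 × 3 = 36.
- Phase 2, 14 weeks with two supervised sessions per week: 14 × 2 = 28.
- Supervised total: 36 + 28 = 64.

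The exercise arm therefore has 64 + 2 = 66 planned occasions and usual care has 2. The Measurements section spreads each assessment over two days. If each day counts as a contact, the figures are 64 + 4 = 68 and 4. These are planned sessions, and actual numbers depend on attendance.

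Unsupervised sessions are left out. Phase 2 has a further 14 × 2 = 28, and Phase 3 has 26 × 4 = 104 by Table 1, but the article does not describe anyone asking about adverse events at them.

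**3. What unequal questioning could do to counts (illustration)**

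The article gives no detection probabilities, so these are assumptions. Let *r* be the chance that a visit interview captures an event and *s* the chance that session questioning captures it, independently of each other. With equal true event rates:

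- Detected in usual care: *r*
- Detected in the exercise arm: 1 − (1 − *r*)(1 − *s*)
- Apparent ratio: [1 − (1 − *r*)(1 − *s*)] / *r*

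| *r* | *s* | Exercise arm | Usual care | Ratio |
|---|---|---|---|---|
| 0.30 | 0.95 | 0.965 | 0.30 | 3.22 |
| 0.30 | 0.80 | 0.86 | 0.30 | 2.87 |
| 0.50 | 0.80 | 0.90 | 0.50 | 1.80 |
| 0.90 | 0.50 | 0.95 | 0.90 | 1.06 |

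Over *r* from 0.3 to 0.9 and *s* from 0.5 to 0.95, the ratio runs from 1.06 to 3.22 with no true difference. Well-remembered events such as hospital admissions belong near the low end, and minor symptoms nearer the high end. The relatedness condition comes on top of this.

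**4. Does anything else in the article offset this?**

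Medical records are used for cancer and treatment variables (Health and treatment-related information) and for transfusion and erythropoiesis-stimulating agents (Biochemical and blood-based markers). Hospitalisations and cardiac events are not named in either place. No interim questioning of controls is described.

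**The case against.** The strongest reply is that the article plans no between-arm safety comparison. Safety is not among the primary, secondary or exploratory outcomes, and the statistical section specifies no AE analysis. Read as surveillance for harm from the exercise and the tests, the section is sensible: asking at each session is appropriate, and any possibility of a relation is a low threshold. This stands. It limits the point to what the data can support, but it does not make the counts comparable.

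Several stronger readings are tempting, and the article does not support them.

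- *That cardiac or treatment effects of exercise would go unseen.* Echocardiography, exercise CMR, troponin-I and BNP are scheduled alike in both arms, and imaging is quantified by researchers blinded to subject identity. Chemotherapy dose intensity is collected, and the effect on treatment received is an exploratory outcome. What is lost is narrower: clinical events judged unrelated are not classified as AEs. The article does not say whether such events, if mentioned at interview, are noted anywhere.
- *That 66 against 2 measures the bias.* It counts occasions of asking. One interview can cover a whole interval, and a death or admission does not need repeated prompting to be found.
- *That the imbalance reaches 198 against 2.* That total, 36 + 56 + 104 + 2, needs AE questioning at unsupervised sessions. The ET adherence and attendance section describes participants logging attendance and dose, with no mention of adverse events.
- *That unblinded staff judge relatedness.* The article says "Participants, care providers and outcome assessors will not be blinded to group allocation", but it does not say who makes this judgement. Open-label influence is possible, not stated.

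**Conclusion.** The point holds in limited form. By the stated rules, AE and SAE counts can describe intervention-related harm within the exercise arm. They cannot support a fair statement about safety between the arms. Both causes are in the text: a definition that a control's event can meet only through a testing procedure, and at least 64 planned supervised sessions of extra questioning in one arm on top of two shared time points.

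The size of any resulting distortion cannot be derived from the article. The range of 1.06 to 3.22 rests entirely on assumed detection probabilities and covers the questioning frequency only.

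The primary outcome, the sample size and every stated analysis are unaffected. This is an inexpensive improvement to the safety data, not a flaw in the main comparison. It is best made early, because the trial was recruiting at submission and events not recorded at the time are hard to recover.

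**What to change.** 1. At the 4- and 12-month interviews already held in both arms, record all untoward events since randomisation or the previous interview, regardless of cause. At minimum, record all that meet the seriousness criteria, including hospitalisations and cardiac events.
2. Record relatedness to a study procedure or the exercise intervention as a separate attribute, and state who judges it.
3. Base any by-arm safety table only on these commonly collected events.
4. Keep the questioning at training sessions, and report what it finds separately and descriptively for the exercise arm.

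**Cost.** An amendment to one paragraph, a form change and modest extra recording, with no new visits or staff. Recording every event in women on chemotherapy will be more work than recording serious events alone, which is why the serious-only minimum is offered. Checking hospitalisations against medical records would be a small addition to the current abstraction, as it is not named as part of it.

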### Data management

Participants will have their personal information de-identified using a code available only to members of the research team. Electronically-stored data will be double entered in a de-identified format onto a secure online data management system (REDCap, Vanderbilt University, Nashville, USA). Frozen blood samples will be kept indefinitely in a re-identifiable format in a − 80 °C freezer. There will not be a formal data monitoring committee for this study, however the study team will meet monthly to review study progress and data will be checked at regular intervals during the study.

### Sample size calculation and statistical analysis

Our sample size of 100 subjects will address Aims 1 and 2 with sufficient compensation for expected attrition of 10% based on our previous pilot work in which two women withdrew (moved interstate and severe treatment related illness) [32]. Primary and secondary analyses will be analysed on an intention-to-treat basis in line with the CONSORT guidelines. Participants who discontinue the intervention will still be asked to attend follow-up evaluations and their results will be included within the intention-to-treat analysis. The significance level for statistical analysis will be set at 5%.

The sample size estimations for Aim 1, that significantly fewer patients undergoing exercise therapy will be functionally disabled at 12 months, are based on our pilot study in which 29% of the total cohort met this criteria at treatment completion and in which there was a 7-fold greater proportion of functional disability in the usual care arm (Usual care: 50% vs Exercise Training: 7%) [32]. In the current proposal, we have used a conservative 24% incidence of functional disability (cf. 29% in the pilot) and three-fold difference between groups (cf. 7-fold in the pilot) [32]. To detect a 36% vs 12% difference in the prevalence of functional disability, 45 women in each group is required (β = 20%, α = 5%). Generalised linear mixed models (GLMMs) with participants as the random effect, time as a repeated measures, and group and group-by-time interactions as the fixed effects, will be used to evaluate the differential effects of the intervention on the incidence of functional disability and additional secondary outcomes. All data will be analysed unadjusted, and adjusted for models including potentially important covariates found to be significantly different between groups at baseline that could explain residual outcome variance. No imputation will be performed for subjects who have missing data due to dropping out of the study. Pre-planned per-protocol analysis including only subjects attending > 66% of the planned exercise sessions will explore the influence of exercise adherence on the primary and secondary outcomes.

The second primary aim of the study is to compare the predictive ability of standard-of-care measures (LVEF) with peak Qc measured by ExCMR in identifying women who will meet criteria for functional disability at 12 months. A multivariate regression will be used with five variables entered (age, LVEF, GLS, study group and peak Qc). The analysis will be stratified for group allocation (usual care vs exercise training) to account for the potential influence of the exercise intervention on the incidence of functional disability at 12-months. The sample size estimated for such an analysis can be calculated as 90 women (50 + 8 x no. of variables) using the method suggested by Green [74].

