### Measurements

All measures will be collected at baseline (within 2 weeks of the initiation of AC), following the completion of AC (4-months) and again at 12-months following the initiation of AC. Assessments will be performed at the Baker Heart and Diabetes Institute clinical research facility over two non-consecutive days. Testing session 1 will be conducted prior to chemotherapy, whilst it will be the aim to complete session 2 within the first 2 weeks of starting AC. Session 1 will consist of the resting echocardiography and blood pressure, cognition testing, questionnaires, CPET, blood sample, ExCMR and training in the use of the accelerometer devices for measurement of habitual physical activity. Tests completed during session 2 will include strength and physical function testing and dual-energy x-ray absorptiometry (DXA) scanning.

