### Primary and secondary outcome measures

The primary outcome for this study will be the prevalence of functional disability (defined as VO_2_peak ≤ 18.0 mL/kg/min) measured via CPET at 12 months. The predictive ability of standard-of-care versus novel cardiac reserve measures will be addressed by comparing LVEF assessed via 3-dimensional (3D) echocardiography to cardiac reserve assessed via exCMR. For the purposes of this study, impaired cardiac reserve will be defined as a < two-fold increase in Qc from rest to peak exercise [33]. Impaired LVEF will be defined as a LVEF < 53% which is in line with current cardio-oncology guidelines [14, 15, 17].

Secondary outcomes will include changes in cardiopulmonary fitness and cardiac reserve, along with indices of resting cardiac structure and function, vascular stiffness, biochemical and blood-based markers of cardiovascular function, total- and regional body composition, bone mineral density of the lumbar spine and femoral neck, muscle strength, physical function, habitual physical activity, cognitive function, and multidimensional quality of life.

Additional exploratory outcomes will include the association between changes in cardiopulmonary fitness with indices of cardiac (cardiac reserve) versus non-cardiac factors (central vascular stiffness, haemoglobin concentration, lower body lean body mass, skeletal muscle composition of the thigh). The study will also explore the effect of the intervention on treatment-related variables including the dose of treatment received and response to neoadjuvant therapy.

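### For the continuous secondary outcomes, a common baseline mean or routine adjustment for the baseline value would cut the variance of the 12-month effect by about 10–25% at no cost (assumed baseline-to-12-month correlation 0.8–0.5)

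*Protocol article*

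**What the plan says.** Under Sample size calculation and statistical analysis, the Protocol article names one family of models, "with participants as the random effect, time as a repeated measures, and group and group-by-time interactions as the fixed effects". It is to evaluate "the differential effects of the intervention on the incidence of functional disability and additional secondary outcomes", so it also covers the continuous outcomes.

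The same section plans each analysis twice: unadjusted, and "adjusted for models including potentially important covariates found to be significantly different between groups at baseline". No routine adjustment for the baseline value of the outcome is stated, and nothing says that the arms share a baseline mean.

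The Measurements section makes baseline one of three repeated occasions: "All measures will be collected at baseline (within 2 weeks of the initiation of AC), following the completion of AC (4-months) and again at 12-months". Randomisation and blinding gives the order of events: "Following baseline testing, each participant will be randomly allocated (1:1 ratio) to the intervention or control group". Primary and secondary outcome measures words these outcomes as changes: "Secondary outcomes will include changes in cardiopulmonary fitness and cardiac reserve, along with indices of resting cardiac structure and function".

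**The concern.** If baseline is a row in the outcome vector, and both group and group-by-time are fixed effects, the model estimates a separate baseline mean for each arm. The 12-month group-by-time term is then the difference between arms in mean change from baseline. Because allocation comes after baseline testing, any baseline gap between the arms is chance. The model spends information estimating a quantity whose true value is zero, and subtracts the whole of that chance gap from the 12-month comparison. A baseline-adjusted analysis subtracts only the part that the baseline-to-12-month relation supports.

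The covariate rule does not repair this. Even if the baseline outcome counted as a covariate, it would enter only when a significance test on a randomised comparison happened to reject. The gain in precision comes from the correlation between baseline and outcome, not from whether the arms differ by chance.

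At stake is precision for the treatment effect on VO2peak, cardiac reserve and the other continuous secondary outcomes, in a trial that expects about 90 evaluable women.

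**Working it through.** **Inputs from the article.** Three visits (baseline, 4 months, 12 months); baseline before randomisation; 100 women with 10% expected attrition, so 100 × 0.90 = 90, or 45 per arm. **Assumed.** Complete data, equal SD s at baseline and 12 months, and a baseline-to-12-month correlation r. The article gives no correlation or SD for any continuous outcome, so a range of r is shown.

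**The plan's own figure.** The only sample-size figure for the treatment comparison is 45 per group for 36% versus 12% at 80% power and 5% alpha (two-sided assumed). With unpooled variances, (1.960 + 0.842)² × (0.36×0.64 + 0.12×0.88) / 0.24² = 45.8, so 46, which agrees to within one woman. It concerns the binary primary outcome and has no bearing on this point beyond supplying n.

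**Step 1: contrast as planned.** With arm-specific baseline means, the variance contributed by each arm to the 12-month contrast is

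2s²(1 − r)/n.

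**Step 2: common baseline mean, or baseline as covariate.** The variance contributed by each arm becomes

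s²(1 − r²)/n.

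**Step 3: ratio.** (1 − r²) / [2(1 − r)] = (1 + r)/2. The planned confidence interval is wider by the factor √[2/(1 + r)].

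| r | variance multiplier (1+r)/2 | variance reduction | planned CI wider by |
|---|---|---|---|
| 0.3 | 0.65 | 35% | 24% |
| 0.5 | 0.75 | 25% | 15.5% |
| 0.6 | 0.80 | 20% | 11.8% |
| 0.7 | 0.85 | 15% | 8.5% |
| 0.8 | 0.90 | 10% | 5.4% |
| 0.9 | 0.95 | 5% | 2.6% |

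**Step 4: check in the three-visit model.** Generalised least squares with 45 per arm, s = 1 and equal correlations between visits gives these standard errors for the 12-month effect:

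- r = 0.5: 0.211 with free baseline means, 0.183 with a common one; (0.183/0.211)² = 0.75.
- r = 0.8: 0.133 and 0.126; the squared ratio, before rounding, is 0.90.

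Both match the formula.

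**Step 5: in numbers of women.** The reciprocal of the multiplier gives the equivalent increase in sample size: 1/0.75 = 1.33, 1/0.85 = 1.18 and 1/0.90 = 1.11. That is 33%, 18% and 11% more women for r = 0.5, 0.7 and 0.8.

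**Step 6: unequal variances.** With SDs s₀ and s₁₂, the change-score variance minus the adjusted variance is s₀² + s₁₂² − 2r·s₀s₁₂ − s₁₂²(1 − r²) = (s₀ − r·s₁₂)², which is never negative. The size of the gain depends on the equal-variance assumption; its direction does not.

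**The case against.** The strongest reply is that nothing here is an error. Group plus group-by-time is a conventional repeated-measures specification. With baseline taken before randomisation, the difference in change is unbiased and its test is valid. It also fits secondary outcomes that are worded as changes. All of this stands. What it leaves untouched is that the baseline-adjusted contrast targets the same 12-month effect, since the true baseline means are equal, and does so with smaller variance. The reply also notes, correctly, that 10–25% is on the variance scale and comes from an assumed range of r, and that the article makes no power claim for these outcomes.

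A reader might infer something stronger: that the visits are linked only through the participant random effect, so that the 12-month standard errors are wrong. Under that reading the arithmetic is real. A random intercept forces equal variances and equal correlations. With equal variances and correlations of 0.8, 0.8 and 0.6 for 0–4, 4–12 and 0–12 months, the model-based SE is √[(1 − 0.733)/(1 − 0.6)] = 0.82 of the true one. With 0.6, 0.6 and 0.8 it is √[(1 − 0.667)/(1 − 0.8)] = 1.29 of it. With exchangeable visits it is exactly right.

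The document does not establish that reading. The same sentence also treats time as a repeated measure, which can denote a residual covariance across visits, and with an unstructured one the problem does not arise. The structure is not named, but a condensed article may leave that to the analysis plan. The correlations above are assumptions, and they pull in opposite directions.

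**Conclusion.** This is a free improvement. As described, the model appears to leave the baseline means free by arm and plans no routine use of the baseline value, so the 12-month effect on a continuous secondary outcome is a difference in change. That is unbiased but less precise than it need be.

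Over the assumed range of r, 0.5 to 0.8, the loss is moderate; it is small if r is near 0.9. The figures rest on complete data, equal variances, the group-by-time contrast being the effect reported, and baseline measurement preceding allocation as the article states.

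The point does not extend to bias, to invalid tests, or to the binary primary outcome and its 45 per group. It does not show that the planned error bars are wrong.

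**What to change.** For the continuous secondary outcomes, state that both arms share one common baseline mean in the repeated-measures model. Alternatively, include the baseline value of the outcome as a covariate in every model, whatever any baseline significance test shows. Specify separate treatment effects at 4 and 12 months, with the 12-month effect as the main contrast. For any measure actually taken after allocation, the constraint should not be imposed.

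An unstructured 3 × 3 covariance over the three visits is a sensible accompanying choice. Naming it would also settle how the repeated-measures phrase is to be read.

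The cost is a change of analysis text. No new data, visits or participants are needed. The common mean removes one parameter, and the unstructured covariance has six parameters against two for a random intercept, four more per outcome, which about 90 women with three visits can support.

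### The adjusted model takes its covariates from baseline significance tests, so chance sets the adjustment and the randomisation strata and continuous baseline VO2peak are almost never included

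*Protocol article*

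**What the plan says.** All of this is in the protocol article.

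- **Covariate rule** (Sample size calculation and statistical analysis): "All data will be analysed unadjusted, and adjusted for models including potentially important covariates". The set is limited to "potentially important covariates found to be significantly different between groups at baseline". Two conditions are attached: the covariates must differ significantly between arms at baseline, and they must be capable of explaining remaining variation in the outcome.
- **Model for the exercise effect** (same section, called Aim 1 there): a generalised linear mixed model "with participants as the random effect, time as a repeated measures, and group and group-by-time interactions as the fixed effects". No stratification factor and no baseline VO2peak term is named. Age is named only in the regression for the prediction aim.
- **Randomisation** (Randomisation and blinding): 1:1, "participants stratified by age (< 60 or ≥ 60 years) and human epidermal growth factor receptor 2 (HER2) status", in blocks of two and four.
- **Primary outcome** (Primary and secondary outcome measures): "prevalence of functional disability (defined as VO_2_peak ≤ 18.0 mL/kg/min) measured via CPET at 12 months". VO2peak is also measured at baseline and at 4 months (Measurements).
- **Primary analysis**: the section does not say whether the unadjusted or the adjusted result is primary.

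**The concern.** Adjustment is useful when a covariate predicts the outcome. A baseline p-value does not measure that. It tests whether random allocation produced an imbalance, and under valid randomisation the answer is known to be chance. Making significance a condition of entry therefore keeps out a strong predictor that is well balanced, which is the usual case.

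Two kinds of variable are affected most. The stratification factors are balanced by design, so the rule cannot realistically admit them and the analysis does not follow the randomisation scheme. VO2peak at baseline is the continuous measurement whose 12-month value is cut at 18.0 to form the primary outcome, yet it enters only by accident.

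At stake are precision, in a trial sized with little to spare, and a clear primary result. As written, the adjusted model is settled after the arms have been compared at baseline, and it stands beside an unadjusted result with no stated priority.

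**Working it through.** **1. The plan's own figure.** Inputs from the sample size section: 36% versus 12%, power 80%, alpha 5% (two-sided assumed, since sidedness is not stated). With unpooled variance:

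n = (1.960 + 0.842)² × (0.36×0.64 + 0.12×0.88) / 0.24² = 7.849 × 0.336 / 0.0576 = 45.8 per arm.

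This rounds up to 46, close to the stated 45. The pooled-variance formula gives 49, and by that formula 45 per arm has 77% power. The 10% attrition allowance checks: 90 / 0.90 = 100.

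**2. How often chance admits a covariate.** Each test at 5% selects a given covariate in 5% of trials. For k independent candidates, P(at least one) = 1 − 0.95^k: 23% for k = 5, 40% for k = 10, 64% for k = 20. The article does not give k.

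**3. Why the strata are not admitted.** Blocks of at most four limit the imbalance within a stratum to 2. Each level of a factor spans two strata, so its arm counts differ by at most 4. If 20 of 100 women are HER2-positive (assumed), the worst split with 50 per arm is 12 versus 8:

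χ² = 100 × (12×42 − 8×38)² / (50×50×20×80) = 100 × 200² / 4,000,000 = 1.0, against a critical value of 3.84.

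In 4000 simulated trials (100 women, 20% HER2-positive, age mean 53 and SD 9, all assumed), neither the age stratum nor HER2 was ever significant. Continuous age was significant in 0.5%.

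**4. Power given up by not adjusting for baseline VO2peak.** Simulation: 45 per arm; a latent normal 12-month VO2peak cut to give 36% and 12%; logistic likelihood-ratio test at 12 months; 1500 runs per row. The Monte Carlo standard error of a single power near 80% is √(0.8×0.2/1500) = 1.0 point. The correlation r between baseline and 12-month VO2peak is an assumption.

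| r | Unadjusted | Adjusted, pre-specified | Plan's rule | Baseline VO2peak selected |
|---|---|---|---|---|
| 0.3 | 79.7% | 81.9% | 80.1% | 5.1% |
| 0.5 | 80.3% | 84.1% | 80.5% | 5.4% |
| 0.7 | 77.3% | 89.6% | 78.4% | 4.0% |
| 0.8 | 78.7% | 94.1% | 80.4% | 5.0% |

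Repeat runs gave 79% to 80%, 82% to 86%, 78% to 90% and 80% to 94% for the same four correlations. With the two strata also in the model (assumed non-prognostic), the gain was 1 point at 0.3, 2 at 0.4 and 5 at 0.5.

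**5. Does the repeated-measures model already use baseline?** If baseline disability status is the first repeated outcome, it enters in dichotomised form. A marginal (GEE) approximation with baseline and 12 months only (400 runs per setting, r 0.5 to 0.8, baseline prevalence 15% or 24%) gave these powers:

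- group-by-time test: 56–78%
- 12-month contrast: 72–79%
- model forcing a common baseline across arms: 76–88%

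Without that constraint there was no gain over the simple unadjusted comparison.

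**6. Type I error.** Under no effect (24% in both arms, r 0.5 and 0.7), the plan's rule rejected in 4.1% and 5.0% of trials. Counting either the unadjusted or the adjusted result as a success, with baseline VO2peak always in the adjusted one, gave 7.1% and 8.5%.

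**7. Events available.** 45×0.36 + 45×0.12 = 16.2 + 5.4 = 21.6, about 22. With group and three covariates that is 21.6 / 4 = 5.4 events per parameter.

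**The case against.** The strongest reply has five parts.

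- **The rule is not indiscriminate.** A reader might infer that anything crossing 5% is adjusted for. The article also requires that a covariate be potentially important and able to explain outcome variation. That stands. The fault is that significance is required in addition.
- **Baseline is probably not discarded.** With time as a repeated measure and assessments at baseline, 4 and 12 months, baseline is most naturally the first outcome row. For continuous secondary outcomes the model then already uses the baseline value. This also stands, but for the primary outcome only the dichotomised status is used, and step 5 shows no gain from it.
- **Large power gains rest on an assumption.** A reader might quote a rise from about 79% to 86–96%. That needs a correlation of 0.6 to 0.8, which the article does not support, with chemotherapy, later treatment and a year of training in between. It also comes from a single-time logistic model, not the planned mixed model.
- **Leaving out the strata does not invalidate inference.** Omission usually makes the analysis conservative. No loss has been quantified for age or HER2, and HER2 may predict little. For the strata, the argument is that the analysis should match the design.
- **An analysis plan not shown may name the primary result, and the unadjusted analysis is always run.** This is a fair limit on that part of the point. It does not rescue the selection rule, which the article itself states.

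**Conclusion.** The point holds as a recommended change, not as a flaw that invalidates the trial. The rule makes chance imbalance the entry condition. It effectively never admits the stratification factors, admits continuous baseline VO2peak in about one trial in twenty, and leaves the adjusted model open until the arms have been compared.

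A reader might infer that the rule inflates the false-positive rate. The check does not support this: rejection under the rule was 4–5%. The excess, 7–8.5%, arises only if whichever of the two results is favourable is reported. The article leaves that possible by naming no primary result, but does not propose it.

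The precision at stake is about 1 to 4 power points at correlations of 0.3 to 0.5 (5 in one set of runs) and about 12 to 15 at 0.7 to 0.8. These figures assume 45 analysed per arm, the planned 36% and 12%, a two-sided 5% test and a logistic model at 12 months. Nearly all of the gain comes from baseline VO2peak, not from the strata.

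**What to change.** Delete selection by baseline tests and state the following instead.

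- **Primary model for the exercise effect:** adjusted for age stratum (<60/≥60), HER2 status and continuous baseline VO2peak. Outcomes are at 4 and 12 months only, and the 12-month group contrast is the primary estimate. Baseline must not also be an outcome row, because disability at baseline is fully determined by baseline VO2peak.
- **Continuous secondary outcomes:** adjusted for the strata. Either use the outcome's own baseline as a covariate with post-baseline rows only, or keep baseline as a repeated measure with a common mean across arms.
- **Unadjusted results:** supportive.

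The cost is a few sentences and no new data, since all the variables are already collected. The trial was recruiting at submission, so the change could be made before outcomes by arm are examined.

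There is a small downside. With about 22 events the covariate list should stay this short, and a small-sample or penalised likelihood method should be used: the ordinary likelihood-ratio test for the fully adjusted model rejected in about 5–6% of null trials in one set of runs and up to 7.7% in another. The adjusted odds ratio is also conditional on the covariates, so a standardised risk difference can be reported beside it.
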